### Ethics approval and consent to participate

The researcher obtained the code of ethics to carry out this research (IR.SBMU.PHARMACY.REC.1404.067) from the Ethics Committee of Shahid Beheshti University of Medical Sciences, registered in ClinicalTrials.gov under the code NCT07099326, and received permission to conduct the research from the Research Vice-Chancellor of Shahid Beheshti University of Medical Sciences All the participants will be provided written informed consent and will be notified of the right to withdraw from participation at any time during the research until publication. Data confidentiality will be ensured, and the results will be provided to the participants at their request. Also, we confirm that all experiments will be performed per the relevant guidelines and regulations. The ethical principles of the Declaration of Helsinki will be followed throughout the study.

### Status and timeline of the study

Recruitment for the participants is planned to begin in September 2025. After recruiting, the intervention and its follow-up are expected to be completed by February 2026. The data analysis will be conducted in February 2026, and the manuscript will be completed by March 2026. The SPIRIT schedule of enrollment, interventions, and assessments is presented in Fig 1.

**Fig 1 pone.0334498.g001:**
[figure not shown]
SPIRIT schedule of enrolment, interventions, and assessments. -t_1_ = Immediately Before Allocation, t_1_ = Immediately Before Intervention, t_2_ = Immediately After Intervention, t_3_ = 1-Month After Intervention, t_4_ = 3-Month After Intervention, INT = Intervention Period, 0 = Allocation Period, t_x_= After the End of Follow-ups.

### Interventions

#### Educational content.

A comprehensive literature review will be conducted to identify the optimal educational content. This process will involve the extraction of relevant articles, books, programs, and clinical and academic guidelines. A systematic search will be conducted of English-language databases, namely PubMed, Scopus, Web of Science, and Embase. SID, Magiran, and Iranmedex will also be explored among Persian-language databases. The searches will be performed using keywords including “Patient Activation,” “Treatment Adherence,” “Hemodialysis,” as well as their synonyms and alternative terms. The search time-frame will span from the inception of each database until June 2025.

Subsequently, the initial program content will be developed and then evaluated. Five dialysis-experienced nurses will assess the program’s comprehensiveness through a checklist and pinpoint areas needing further development; their feedback will be incorporated into the final version of the program. After the educational program is finalized, its content will be validated by ten nursing faculty members and nephrologists. This panel will be purposively selected to validate the program content. Eligibility criteria will include an academic appointment in nephrology nursing, dialysis care, or patient education; at least five years of relevant clinical or teaching experience; and prior involvement in curriculum development or content validation. Faculty will be recruited through institutional records and professional networks, and all will provide independent ratings of content relevance and clarity using a standardized checklist. Based on the experts’ evaluations, supplementary materials will be produced, and necessary revisions will be made.

A Content Equivalence Checklist will be developed by the research team and independently verified by two subject-matter experts. The checklist will include items such as (a) verifying each predefined knowledge unit is included, (b) following the same clinical case vignettes, (c) using equivalent terminology and explanations, and (d) maintaining consistency in visual aids and key messages. Both video versions will be pilot-tested against this checklist, and inter-rater agreement will be reported. Any discrepancies will be resolved through consensus before final approval.

We will prospectively estimate the typical contact time under interventions and usual care to facilitate transparent comparison of exposure across arms. All actual contact times (minutes per session and number of contacts) will be logged prospectively for every participant and reported in the primary results.

### Interactive video education arm

The educational intervention will be delivered in two sequential phases over a total duration of six hours. A cohort of participants will be enrolled and organized into groups of five, each group facilitated by a certified instructor with expertise in interactive video pedagogy.

#### Phase 1: Interactive video–based instruction (10 × 30‑minute modules).

Participants will log in individually to the secure platform to complete ten interactive modules focused on ESRD pathophysiology and alternative treatment modalities. One 30‑minute module will be released per day. Context-sensitive pop‑up queries will prompt participant responses during each module, and divergent answer pathways will dynamically determine subsequent scenario content. Embedded multiple‑choice assessments will further evaluate comprehension; all responses will be recorded in real time via the learning management system for instructor review. Before module commencement, participants will undergo a standardized orientation session to ensure operational proficiency with the platform and clarity regarding study procedures.

#### Phase 2: Consolidation and synthesis workshop (1 hour).

Upon completing the interactive modules, participants will reconvene in their assigned groups for a one‑hour, instructor‑led workshop. The instructor will facilitate critical discussion of the scenarios, guide the extraction of salient clinical concepts, and synthesize group findings. This workshop will emphasize higher‑order cognitive processing of disease complexity and integration of theoretical constructs. The session will conclude with targeted didactic feedback to reinforce key learning objectives and enhance long‑term knowledge retention.

### Conventional video education arm

The educational intervention will be delivered in two sequential phases over a total duration of six hours. Participants will be enrolled and organized into cohorts of five participants, each facilitated by an experienced instructor conversant with video-based teaching methods.

#### Phase 1: Conventional video-based instruction (10 × 30-minute modules).

Participants will access the secured learning platform at https://spotplayer.ir/ to view ten pre-recorded video modules detailing ESRD pathophysiology and alternative treatment modalities. One 30-minute module will be released daily. Videos will be streamed in their entirety without interactive elements; the instructor will oversee module completion and address any technical queries but will not interject during playback.

#### Phase 2: Consolidation and synthesis workshop (1 hour).

After completing all video modules, participants will reconvene in their assigned cohorts for a one-hour instructor-led workshop. The instructor will facilitate group analysis of the presented content, guide extracting key clinical concepts, and synthesize collective insights. This session will foster critical reflection on disease complexity and integration of theoretical knowledge. The workshop will conclude with targeted didactic feedback to reinforce the principal learning objectives and support retention.

### Control group (Usual care)

Participants in the control arm will receive the standard educational practices routinely implemented at each site. Specifically, this will include:

**Nurse-led education:** Registered nurses in the dialysis unit will provide face-to-face instruction on disease management and self-care behaviors.**Educational pamphlets:** Participants will be given institution-approved printed materials covering key aspects of ESRD and alternative therapies.**Nurse follow-up:** A dedicated follow-up nurse will provide regular monitoring, either in person or via telephone, to reinforce educational information, address inquiries, and assess adherence to suggested self-care methods.

All procedures will be conducted according to each hospital’s established protocols and within the time-frame of the three-hour educational session allocated to the intervention arms (Fig 2).

**Fig 2 pone.0334498.g002:**
[figure not shown]
Interventions schematic details. A: Interactive Video, B: Conventional Video, C: Usual Care.

### Randomization, allocation concealment, and implementation

Participants will be randomly assigned to one of the three study arms (1 = interactive video, 2 = conventional video, 3 = usual care) in a 1:1:1 ratio.

### Sequence generation

An independent biostatistician, who is not involved in patient enrollment or intervention delivery, shall produce a computer-generated randomization list. Randomization will be stratified by hospital and dialysis shift to ensure balanced assignment across recruitment sites. Within each stratum, variable block sizes—such as 3, 6, and 9—will be employed to reduce predictability while maintaining allocation equilibrium. The sequence shall be generated utilizing the ‘blockrand’ package in R (version 4.x) with a reproducible seed.

### Allocation concealment

Assignments will be implemented through a centralized, password-protected web-based randomization system to maintain allocation concealment and prevent selection bias. The allocation will only be revealed after participant eligibility and baseline assessment have been completed. If a central system is unavailable, sequentially numbered, opaque, sealed envelopes, prepared by the independent statistician, will be used following best practices [39].

### Implementation

The allocation sequence shall be generated and stored securely by the independent statistician. Research nurses responsible for screening and enrolling participants cannot access the sequence. After confirming eligibility and obtaining informed consent, the enrolling investigator will log into the central randomization platform to acquire the group assignment. Intervention facilitators and outcome assessors shall remain blinded to the randomization list, and outcome assessors shall be blinded to group allocation.

### Blinding

Given the nature of the educational interventions (interactive video, conventional video, and standard nurse-led education), neither participants nor instructors can be blinded to group assignment. Outcome assessors will be blinded to intervention allocation when administering follow-up questionnaires and extracting clinical and adherence data from medical records. The trial’s statistical programming team will conduct all analyses on a de-identified dataset in which intervention arms are labeled as Group A, B, or C. The key linking these labels to the actual interventions will be held securely by the trial statistician and not revealed until after the primary analyses are complete.

### Permissible Unblinding

Unblinding of data analysts will only occur under exceptional circumstances in which knowledge of the participant’s educational assignment is required to address a serious concern. The principal investigator must receive all unblinding requests in writing and will subsequently consult with the Data and Safety Monitoring Board. If approved, the trial statistician will disclose the specific participant’s allocation from the master randomization file. The study records will document all unblinding events, including the justification, date, and personnel involved.

### Contamination control and monitoring

Considering the standard setting of dialysis units and the potential for information exchange among patients, there exists an intrinsic risk of contamination between study groups. A combination of procedural and analytical strategies will be implemented to address this concern.

### Secure delivery of video content

Educational videos associated with individual user accounts shall be provided via a secure, password-protected online platform. Access and viewing durations will be systematically recorded for each participant to uphold integrity and identify any potential unauthorized cross-use.

### Separate workshops and facilitators

Consolidation workshops shall be scheduled separately for each study arm, with dedicated facilitators appointed to each group. Facilitators will be instructed to refrain from sharing educational materials across groups.

### Monitoring of cross-exposure

At each subsequent follow-up appointment, participants will be inquired as to whether they have been exposed to educational materials from other study groups (e.g., by watching videos or receiving information from peers). These self-reports will be utilized to estimate the rate of contamination.

### Sensitivity analyses

If the observed contamination rate exceeds 20%, the potential for dilution of intervention effects will be clearly reported. Sensitivity analyses will be performed to evaluate the robustness of findings under different assumptions about contamination.

### Strategies to mitigate instructor bias, workshop imbalance, and participant adherence

Several fidelity procedures will be implemented to minimize potential instructor/facilitator bias and ensure that observed differences are attributable to the interactive video components rather than variations in facilitator performance.

A facilitator manual will be developed, containing the exact script for each workshop, learning objectives for each section, guiding questions, and a structured activity timeline. A fidelity checklist will be completed by the facilitator after each session and verified by the study monitor; checklist items will include adherence to the script, duration of response time, avoidance of supplemental content, and documentation of participant attendance. All facilitators will undergo standardized training and competency testing before study initiation, with a required passing score of ≥85% on the procedural assessment. In addition, selected sessions will be audio- or video-recorded for independent fidelity review by three external evaluators blinded to allocation, and corrective feedback will be provided during the first ten sessions.

Participant engagement with the pre–recorded videos will be supported by automated SMS or telephone reminders sent one hour before each scheduled module release. Video-access logs within the learning management system will capture start and completion times for each 30‑minute session and quiz completion rates where applicable. Nursing staff in the control arm will analogously document each face-to-face or telephone education encounter’s date, duration, and content.

A per‑protocol definition will classify participants as “treated as planned” if they complete at least 100% of their assigned educational components delivered by certified facilitators (i.e., ten of ten video modules). Participants failing to meet this threshold or whose sessions are conducted by non‑certified staff will be categorized as “not treated as planned.”

### Outcome measures

#### Primary outcome.

Patient activation will be measured using the 13-item Patient Activation Measure (PAM) created by Hibbard et al. [40]. Participants will rate each item on a five-point Likert scale— “strongly disagree” (1), “disagree” (2), “agree” (3), “strongly agree” (4), or “not applicable” (no score)—yielding a raw total score between 13 and 52 [41]. Raw scores will be transformed to a standardized 0–100 scale per the PAM scoring algorithm and classified into four activation levels:

Level 1 (disengaged and overwhelmed): ≤ 47Level 2 (becoming aware of the need for self-management): 47.1–55.1Level 3 (taking action): 55.2–67Level 4 (maintaining behaviors and pushing further): > 67.1

The English-language PAM has demonstrated excellent reliability in nephrology populations (Cronbach’s α = 0.87) [40]. The Persian version of PAM demonstrated a Cronbach’s alpha coefficient of 91% [20]. For this trial, a Persian translation will be produced via forward- and back-translation by a bilingual expert and undergo content validation by ten nursing faculty members. Internal consistency of the Persian PAM will be assessed within our study cohort by calculating Cronbach’s alpha. PAM assessments will be conducted at baseline and at each follow-up visit to evaluate changes in patient activation over time.

#### Secondary outcome.

Patient adherence to prescribed therapy will be evaluated using the End-Stage Renal Disease Adherence Questionnaire (ESRD-AQ), a validated 46-item self-report instrument encompassing five domains: General ESRD Knowledge (5 items), Hemodialysis Attendance (14 items), Medication Compliance (9 items), Fluid-Restriction Adherence (10 items), Dietary Recommendation Compliance (8 items). The items utilize a combination of Likert scales, multiple-choice formats, and dichotomous (yes/no) responses. Total scores range from 0 to 1,200, with higher values reflecting greater overall adherence [42]. The ESRD-AQ has demonstrated excellent psychometric properties: Rafiee et al. (2014) reported a Cronbach’s α of 0.91 and test–retest reliability of 0.85 [43], while Kim et al. (2010) established a content validity index (CVI) of 0.99 [42]. In this trial, the ESRD-AQ will be administered at baseline and at each follow-up visit to quantify changes in patient adherence over time.

Also, in this study, IDWG will be measured as a secondary outcome by weighing patients immediately before connecting to the dialysis machine and right after each HD session, following a set of standardized protocols. All weightings will be performed using a calibrated medical digital scale (calibrated monthly). Patients will always be weighed wearing a standardized light dialysis gown, emptying their bladder beforehand, and refraining from food or drink before weighing. Additionally, all personal items (shoes, bags, jewelry) will be removed before weighing. Trained staff or the researcher will record all measurements at fixed times (before starting and after finishing dialysis) meticulously to ensure data consistency and allow reliable comparison of weight changes throughout the treatment period [24].

### Data collection and management

The principal investigator will oversee trained research assistants in collecting all trial data, which will be gathered via structured and validated instruments. The primary and secondary outcomes will be assessed via self-reported questionnaires completed by participants at baseline (pre-intervention), immediately post-intervention, and at 1–3 months’ follow-up (Fig 3).

**Fig 3 pone.0334498.g003:**
[figure not shown]
Procedural flow of RCT protocol.

Data will be collected in paper-based format at the clinical sites and subsequently entered into a secure electronic database. Double data entry will be employed to minimize transcription errors. All data collectors will undergo a standardized training session before study initiation to ensure uniformity in data collection procedures and administration of outcome measures. A structured questionnaire will be used to collect baseline data, consisting of two main sections:

#### Section 1: Demographic data.

This section considers age, sex, educational level, marital status, employment status, place of residence, duration from CKD diagnosis, duration from HD initiation, and presence of comorbid conditions.

#### Section 2: Clinical data.

Clinical variables will include daily salt intake (in grams), daily urine output (in milliliters), number of HD sessions per week, amount of fluid intake, and any dialysis-related complications. These data will be extracted from the participants’ medical records before the intervention.

### Plans to promote participant retention and complete follow-up

To maximize retention and reduce missing data, the following strategies will be implemented: Research staff will maintain monthly contact with participants via phone or messaging to encourage continued participation and address any technical or logistical challenges. Also, participants will receive automated reminders (SMS or calls) for each video session and follow-up assessment point. Assessments will be conducted during routine dialysis sessions to reduce participant burden. In the event of participant discontinuation or deviation from the intervention protocol, all primary and secondary outcome data will be gathered at the defined follow-up intervals. Reasons for discontinuation or protocol non-adherence will be documented through structured exit interviews. All outcomes will be analyzed under the intention-to-treat principle. Missing data (overall percentage, distribution across arms, and patterns) will be carefully described. If the amount of missing data on the primary outcome is very low (≈≤5%) and there is no evidence of systematic or differential missingness between arms, a complete-case analysis may be reported as the primary analysis, with multiple imputation (MI) used as a sensitivity check. MI will be the primary approach if missingness is higher or shows evidence of association with treatment arm or baseline covariates [44–46]. Imputation models will include all outcome time-points, treatment allocation, baseline covariates, and auxiliary predictors. Appropriate conditional models will be applied by variable type (predictive mean matching for continuous, logistic/multinomial/ordinal regression for categorical). At least *m* = 20 imputations will be generated (increasing *m* if the fraction of missing information is large). Chain convergence will be checked, and each imputed dataset will be analyzed with the pre-specified mixed model (or GEE for longitudinal outcomes). Estimates will be pooled using Rubin’s rules. Robustness will be examined using complete-case analyses, pattern-mixture approaches, and delta-adjustment (tipping-point) sensitivity analyses. Implementation and diagnostics will be conducted in R.

All data will be entered into STATA version 17 and R software using a double-entry method to minimize errors. Coding will follow predefined guidelines, with range and consistency checks applied regularly. The research team will be the only people able to access the data, which will be stored securely on password-protected systems. Paper records will be kept in locked cabinets. Identifiable information will be separated from study data to ensure confidentiality. Data will be retained for five years post-study, after which it will be securely destroyed. A detailed data management plan is available upon request.

### Statistical analysis

The baseline characteristics will be summarized using descriptive statistics (mean ± SD, frequency, and percentage). Primary and secondary outcomes will be analyzed using longitudinal data analysis methodologies, accommodating repeated measures collected at four time points (baseline, immediate post-intervention, one-month, and three-month follow-up) and across three intervention groups. Depending on the attributes and distribution of the dependent variables, consideration will be given to both mixed models for repeated measures (MMRM) and generalized estimating equations (GEE).

MMRM will be applied to model continuous normally distributed outcomes, incorporating fixed effects for group, time, and their interaction, with an appropriate covariance structure to account for within-subject correlations. GEE will be used as an alternative approach, particularly for outcomes with non-normal distributions or when robust population-averaged effects are of interest. MMRM and GEE will be chosen based on model fit and assumptions.

Analyses will be conducted under the intention-to-treat principle. Missing data will be addressed using multiple imputations, assuming they are randomly missing. Effect measures, CI, and a significance level of p < 0.05 will be reported. Adjusted analyses may include relevant covariates, with the primary analysis specified accordingly.

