### Sample size

Due to the absence of previous studies closely matching the design and interventions of the present trial, the sample size calculation will be based on data obtained from a preliminary pilot study that the research team will conduct. A pilot study will be conducted in the same dialysis units as the definitive three-arm trial. It aims to (1) estimate parameters required for sample-size calculation (primary-outcome SD), (2) assess recruitment and retention rates, (3) measure patient adherence and provider fidelity, (4) evaluate methodological contamination, and (5) identify operational or data-quality problems.

The selection of this approach ensures that the sample size possesses sufficient statistical power to identify clinically relevant differences between groups, taking into account the unique features of both the study population and the interventions.

Participants will be screened consecutively using the same inclusion/exclusion criteria as in the primary protocol, provide informed consent, and be randomized to one of three arms. The intervention principles, outcome instruments, and timepoints will be identical to those in the definitive trial. For feasibility-only objectives, approximately 12 participants per arm (36 total) will be recruited [38]; if variance estimation is required, around 35 per arm (105 total) will be targeted [38].

A pilot report will document parameter estimates and operational findings. Pilot outcomes include: Standard Deviation (SD) and 95% Confidence Interval (CI) of the primary outcome, recruitment and retention proportions, adherence categories, fidelity scores from structured checklists, contamination based on self-report and digital access logs, and data-quality indicators (missing data, questionnaire burden, technical issues).

Pilot estimates will inform the definitive sample size, attrition-adjusted recruitment targets, and possible design modifications if contamination is substantial. Any changes to the main trial will be justified, approved, and reported. The sample size will be estimated using the pilot data, with a significance level of 0.05 (two-sided) and a statistical power of 80%. The total estimates will be allocated equally across the three study groups. By relying on pilot data without prior literature, the study design ensures methodological rigor and optimizes resource use while maintaining sufficient power to address the primary research objectives.

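### The model names only group, time and their interaction, and leaves adjustment for baseline PAM, hospital and dialysis shift optional, at a cost in precision

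*Protocol article*

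**What the plan says.** All references are to the protocol article.

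- **Statistical analysis.** Baseline, immediate post-intervention, one month and three months are the four repeated measures. The mixed model is described as "incorporating fixed effects for group, time, and their interaction", with a within-subject covariance structure still to be chosen. On covariates: "Adjusted analyses may include relevant covariates, with the primary analysis specified accordingly". No covariate is named, and neither is a common baseline mean.
- **Sequence generation.** "Randomization will be stratified by hospital and dialysis shift to ensure balanced assignment across recruitment sites".
- **Allocation concealment.** The allocation is revealed only once eligibility and baseline assessment are complete.
- **Sample size.** "The sample size will be estimated using the pilot data", at "a significance level of 0.05 (two-sided) and a statistical power of 80" per cent. The only parameter listed for that calculation is the SD of the primary outcome. No definitive sample size, effect or SD is given.
- **Plans to promote participant retention and complete follow-up.** Imputed datasets are to be analysed with a prespecified mixed model. The only mixed model the article describes is the one above.

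**The concern.** Two sets of variables known before allocation are not secured in the primary model: the baseline value of the outcome and the stratification factors.

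For baseline, when each arm has its own baseline mean, the group-by-time term compares changes from baseline, and a group contrast at one visit compares follow-up values alone. For any correlation strictly between 0 and 1, both are less precise than conditioning on baseline. In a given trial, a chance baseline imbalance also carries into the change scores through regression to the mean.

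For the strata, balancing the arms on a factor and then leaving it out of the model makes the reported standard error larger than the design warrants.

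What is at stake is efficiency: more patients than needed, or less power than intended. Leaving the covariates open also leaves their choice open until a later stage, although the natural candidates are already known.

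**Working it through.** **Inputs from the article:** two-sided alpha 0.05, power 80%, 1:1:1 allocation, four time points, stratification by hospital and shift. There is no definitive sample size or power figure to reproduce.

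**Assumptions (not in the article):** correlation rho between baseline and follow-up PAM of 0.4 to 0.7; strata explaining 5% to 10% of variance; a standardised difference d = 0.5 for illustration only.

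**Step 1: baseline.** For one pairwise comparison with common SD, in units of 2 × SD² / n per arm, the variances are:

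- change contrast (free baseline means): 2(1 − rho)
- follow-up only: 1
- baseline as covariate, or common baseline mean: 1 − rho²

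Adjusted over change is (1 − rho²) / [2(1 − rho)] = (1 + rho)/2. Adjusted over follow-up only is 1 − rho².

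| rho | change | adjusted | adjusted/change | adjusted/follow-up |
|---|---|---|---|---|
| 0.4 | 1.20 | 0.84 | 0.70 | 0.84 |
| 0.5 | 1.00 | 0.75 | 0.75 | 0.75 |
| 0.6 | 0.80 | 0.64 | 0.80 | 0.64 |
| 0.7 | 0.60 | 0.51 | 0.85 | 0.51 |

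**Step 2: does the longitudinal model recover the loss?** Exact generalised least squares variances for three arms by four times with complete data say no. With 35 per arm and compound symmetry at rho = 0.5, the change contrast has variance 0.0571 and the common-baseline-mean contrast 0.0429, a ratio of 0.75. At rho = 0.7 they are 0.0343 and 0.0291, a ratio of 0.85. Under AR(1) with adjacent correlation 0.7, the baseline-to-last-visit correlation is 0.343 and the ratio 0.672, again (1 + 0.343)/2.

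**Step 3: what this means for sample size.** n per arm = 2(1.960 + 0.842)² × factor / d². At d = 0.5 a follow-up-only contrast needs 63 per arm.

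| rho | n, change | n, adjusted | power of change contrast at n = 63 |
|---|---|---|---|
| 0.4 | 76 | 53 | 73% |
| 0.5 | 63 | 48 | 80% |
| 0.6 | 51 | 41 | 88% |
| 0.7 | 38 | 33 | 95% |

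If the sample size is set from the raw PAM SD alone and the effect is then read as the group-by-time contrast, the trial is short of power for rho below 0.5 and larger than needed above it. The adjusted analysis needs fewer than 63 throughout.

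**Step 4: strata.** Let R² be the share of variance in the analysed contrast that the strata explain. Stratified allocation already keeps that share out of the true error, but an unadjusted model leaves it in the reported standard error.

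- Type I error = 2[1 − Phi(1.96/√(1 − R²))]: 4.4% at R² = 0.05 and 3.9% at 0.10.
- Power, where the adjusted test has 80%, = Phi(2.80 − 1.96/√(1 − R²)): 78.5% and 76.9%.

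These figures apply to a follow-up or baseline-adjusted contrast. A stratum effect that is constant over time cancels from a change contrast, so they must not be added to the loss in Step 1.

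**The case against.** The strongest reply is that this is a condensed article: exact model terms are commonly left to an analysis plan, and the text does allow covariates. This stands in part. A reader might infer that the model excludes baseline and the stratification factors; the article does not say so. It lists three effects without calling the list complete, and leaves adjustment open. It also does not state whether baseline means are free or common, nor which contrast is primary; free means are the natural reading of a group main effect, but still a reading. What remains is that the article does state model terms, and those terms are less efficient than an alternative that uses data already collected.

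Other stronger readings are also unsupported:

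- **That baseline PAM is thrown away.** The group-by-time contrast uses it through the change score. It is unused only in a follow-up-only contrast, which the article does not say it will use.
- **That power falls from 80% to 68%.** At rho = 0.5, Phi(2.80 × √0.75 − 1.96) = 0.68, but only if the trial is sized for the adjusted analysis and then analysed by change scores. The article states no such mismatch. If the sample size is set for the analysis actually used, power is 80% and the cost is recruitment.
- **That the result would be biased or produce false positives.** Randomisation keeps the change contrast unbiased, and omitting strata errs on the conservative side.

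**Conclusion.** The point holds as one of efficiency, not validity, and is worth acting on. As described, the model does not secure the precision available from baseline PAM. Read with free baseline means, adjustment would cut the variance and the required sample size by 15% to 30% for an assumed rho of 0.7 down to 0.4 (25% at 0.5). Whether the sponsor pays in patients or in power cannot be settled from the article, because the definitive sample size is still to come from the pilot.

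The strata are secondary: about 1.5 to 3 points of power and a type I error of 4.4% to 3.9% if they explain 5% to 10% of the variance, and little if they explain less. Both ranges are assumptions. The baseline ratio depends only on rho; the strata figures depend on a share of variance that the article gives no means of judging.

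**What to change.** State the primary model as PAM at the three post-baseline visits on arm, visit, arm × visit, baseline PAM, baseline PAM × visit, hospital and dialysis shift. A constrained longitudinal model with a common baseline mean, plus hospital and shift, is an equivalent choice. Name the contrast that carries the primary conclusion. Use the same form for ESRD-AQ and IDWG, each with its own baseline.

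Add the baseline-to-follow-up correlation to the parameters that the pilot reports, and base the definitive sample size on the adjusted variance. The pilot uses the same instruments and time points as the main trial, so the correlation can be estimated without further data. If the smaller, feasibility-only pilot is run, the estimate will be imprecise and a cautious (low) value should be used.

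The cost is a change of wording in the Statistical analysis and Sample size sections and one more line in the pilot report.
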